### Measurement procedure

At patient level, the preferred mode of data collection is by routine outcome monitoring (ROM), an online system by which data on the effectiveness of treatment in everyday clinical practice are systematically collected
[26]. In MHIs not using ROM, graduate students and/or research assistants will use paper and pencil questionnaires to collect data. The results from the graduate students/research assistants are expected to be comparable to the data collected via ROM. ROM also works with assistants to collect data and help participants to understand items/instructions
[26]. Using differential item functioning (DIF)
[27], we will investigate if the findings are indeed comparable, and control for any bias due to difference in data collection in the final analysis. By collecting data either via the ROM or graduate students/research assistants, we aim to reach all newly admitted patients in the participating departments. As the intervention focuses on fostering a working relationship with suicidal patients, the intervention is expected to be most effective during the first month of treatment. Therefore, patients will be assessed directly at admission (T0) and at 3 months after admission (T1) (Figure 
2). If a patient is discharged within 3 months, T1 will be arranged just before discharge. Measurements in the experimental departments will start immediately after all staff are trained. In the control departments, T0 will start when the department is informed of the allocation outcome. All eligible patients will be informed about the study and will be asked to provide written informed consent.

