#### Treatment satisfaction

Treatment satisfaction will be assessed with four items established to measure the quality of therapeutic alliance. The first two items are: ‘How satisfied are you with your therapy?’ and ‘How would you evaluate your relationship with your therapist?’. These two items are rated from 0 to 10. Next, we will assess treatment satisfaction with reference to patients’ suicidal behavior: ‘Was there any attention for your suicidal thoughts during therapy?’ and ‘How did your therapist deal with your suicidal thoughts?’. These two items are scored on a four-point Likert scale ranging from: 1, very well, to 4, very poor. As the questions focus on the patient’s experience, these four items will only be administered at T1.

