#### Cost-effectiveness

Costs incurred by patients during the course of the study will be measured with an adapted version of the Trimbos questionnaire for costs associated with psychiatric illness (TiC-P)
[29]. The TiC-P consists of two parts: part one measures direct medical costs (for example visits to a psychiatrist or a psychologist) and part two measures indirect costs (for example costs due to sick leave and productivity losses while being at work but not functioning optimally). If available, Dutch guideline prices will be used to value resource use
[30]. Medication use will be valued using prices of the Royal Dutch Pharmaceutical Society. Lost productivity costs will be calculated according to the friction cost approach (friction period 154 days) using the mean age- and sex-specific income of the Dutch population
[30]. Costs of the development of the intervention will be based on the salaries of the researchers for the development of the TtT-e program, material costs, implementation costs of the e-learning environment, and the costs of the production losses due to training of multidisciplinary teams.

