#### Statistical analyses

As the study is a design with different levels, all outcomes will be analyzed using multilevel models. Patients are nested within departments (level 1), and departments are nested within MHI centers (level 2). Multilevel models are hierarchal systems that estimate random coefficients and variance components for each level
[33]. Random intercepts will be included in the multilevel models. Data will be analyzed on an intention-to-treat basis.

To examine the hypothesis that suicide ideation in patients of professionals who received the TtT-e program is more likely to be reduced than patients of professionals who did not receive TtT-e, we will compare changes in BSS scores between patients of teams allocated to the intervention with patients of teams in the control group. To examine differences in the number and intensity of suicide attempts, scores on items 20 and 21 of the BSS will be dichotomized (YES/NO, LOW/HIGH) and compared between treatment groups using logistic regression. To examine the effect of the intervention on treatment satisfaction, mean scores of the four satisfaction items between groups will be compared. For the economic evaluation, missing cost and effect data will be imputed using multiple imputation according to the MICE algorithm
[34]. The results of the imputed datasets will be pooled using Rubin’s rules
[35]. Bias-corrected and accelerated bootstrapping with 5,000 replications will be used to estimate 95% confidence intervals around the mean difference in total costs between the treatment groups. Incremental cost-effectiveness ratios (ICERs) will be calculated by dividing the difference in mean total costs between the treatment groups by the difference in mean effects between the treatment groups. Bootstrapping will also be used to estimate the uncertainty surrounding the ICERs, which will be graphically presented on cost-effectiveness planes. Cost-effectiveness acceptability curves will also be estimated. Cost-effectiveness acceptability curves will show the probability that the intervention is cost-effective in comparison with usual care for a range of different ceiling ratios (that is, the willingness to pay for one extra unit of effect)
[36].

Approval was obtained from the Medical Ethics Committee of the VU University Medical Centre, Amsterdam, The Netherlands (registration number: 2011/151). All local medical ethics committees agreed with this approval.

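### The cost difference and the ICER numerator are written as differences in mean total costs with no baseline covariate

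*Protocol article*

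**What the plan says.** Under Statistical analyses, the protocol article sets out the economic evaluation in some detail. Missing costs and effects are imputed with MICE and pooled by Rubin's rules. Bias-corrected and accelerated bootstrapping with 5,000 replications gives "95% confidence intervals around the mean difference in total costs between the treatment groups". The ICER comes from "dividing the difference in mean total costs between the treatment groups by the difference in mean effects between the treatment groups". Cost-effectiveness planes and acceptability curves follow from the same bootstrap. No covariate is named in either definition.

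The same section opens by saying that "all outcomes will be analyzed using multilevel models", with random intercepts, and lists no covariates for any outcome. For the primary outcome, however, it compares changes in BSS between arms, so the T0 value enters there.

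On cost data, the Cost-effectiveness section says: "Costs incurred by patients during the course of the study will be measured with an adapted version of the Trimbos questionnaire". It does not say whether the TiC-P is given at T0. The only restriction to T1 concerns the satisfaction questions: "these four items will only be administered at T1".

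**The concern.** A difference in arm means carries whatever baseline difference exists between the arms. Random intercepts deal with the clustering of costs within departments; they do not remove such a difference. Two features of this design make one plausible.

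- **Heterogeneous departments.** Table 1 runs from crisis units with an average duration of 1 day to an inpatient unit averaging 1,532 days, and the pairs are not all close.
- **Entry after allocation.** Under Measurement procedure, "Measurements in the experimental departments will start immediately after all staff are trained", and control departments start once they have been told their allocation. The Randomization procedure section says that professionals know the arm, and the Inclusion and exclusion criteria leave each patient's entry to the staff. Randomising departments therefore does not guarantee that the patients who enter are alike in the two arms.

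Cost-effectiveness is a stated hypothesis aimed at policy makers. A baseline difference would pass into the cost interval, the ICER, the plane and the acceptability curve. Ignoring a predictive baseline variable also makes the interval wider than it needs to be.

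**Working it through.** **1. The plan's own figure.** The Sample size section gives 423 patients for d = 0.3, alpha 0.05 (taken as two-sided), power 0.80 and a 20% correction for clustering. The t-based total is 352, and 352 x 1.2 = 422.4, which rounds up to 423; the normal formula gives 350 x 1.2 = 420. The figure reproduces, but it is for suicide ideation. The article gives no cost SD, no cost intraclass correlation (ICC) and no correlation r between T0 and follow-up costs. All results below are in cost-SD units and rest on assumed values of r and ICC.

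**2. How far matching helps (Table 1, consecutive rows read as pairs).**
- There are 21 experimental and 22 control departments: 21 pairs and one control inpatient unit (371 days) without a partner.
- 8 of the 21 pairs mix department types, for example experimental inpatient 35 days with control outpatient 240 days, and experimental outpatient 42 days with control inpatient 150 days.
- Four pairs differ in listed main diagnosis: eating disorder with personality, personality with addiction, the crisis category with personality, and schizophrenia with mood disorder NOS.
- Overall the arms are similar in type (experimental v control: inpatient 7 v 8, outpatient 10 v 11, crisis 3 v 2). The extremes are paired with each other: 1,532 with 1,308 days, and 1-day crisis units together in two pairs.
- Average duration is missing for three departments.

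**3. Chance imbalance in T0 costs.** With K departments of m patients, SE = sqrt(4/K x (ICC + (1 - ICC)/m)). The article gives both 43 departments (423/43 = 9.84 patients each) and an average of 20 patients per department, so both cluster sizes are shown.
- K = 43, m = 9.84, ICC 0.2: sqrt(0.0930 x (0.2 + 0.0813)) = 0.162; 95% range ±0.32 SD.
- N = 423, m = 20, ICC 0.2: design effect 1 + 19 x 0.2 = 4.8; sqrt(4 x 4.8/423) = 0.213; ±0.42 SD.
- N = 423 with the article's 20% correction (ICC 0.2/19 = 0.0105): sqrt(4 x 1.2/423) = 0.107; ±0.21 SD.

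The part carried into an unadjusted cost difference is r times the imbalance. At the edge of the middle range (0.32), r = 0.3 to 0.6 gives 0.10 to 0.19 SD. These formulas give no credit for pairing, so they overstate the imbalance to the extent that pairing balances costs. They cover chance only; selection at entry cannot be quantified from the article.

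**4. Precision lost.** Two limiting cases, for r = 0.3 and 0.6:
- Variance shrinks by r² at both patient and department level: width factors sqrt(1 - 0.09) = 0.954 and sqrt(1 - 0.36) = 0.80, so 5% and 20% narrower.
- Only patient-level variance shrinks, at ICC 0.2 and m = 9.84: that part is 0.0813/0.2813 = 29% of the total. Variance falls by 0.09 x 0.29 = 2.6% and 0.36 x 0.29 = 10.4%, so the interval is about 1.3% and 5.3% narrower.

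Together this is roughly 1% to 20% of interval width.

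**The case against.** The strongest reply is that the article never calls the difference unadjusted. A mean difference can be a model-based estimate, multilevel models are announced for all outcomes, covariates are commonly left to the analysis plan, and the economic results are to be reported separately. This stands in part: a reader might infer a deliberate choice against adjustment, and the text does not show one. But the section goes beyond silence. It fixes the imputation, the bootstrap, the interval and the numerator formula for costs, and it brings T0 into the BSS comparison but not into this one. If an unseen plan does adjust, the published definition needs bringing into line.

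Second, T0 cost data are only implied, since the cost section speaks of costs during the study. This also stands. It limits the preferred covariate but not the point. QALYs by area under the curve need EQ-5D at T0, and BSS change needs BSS at T0, so baseline covariates exist either way.

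Third, a reader might conclude that resource-use differences older than the training are credited to it. The design does not support this. Patients are assessed at admission, after staff have been trained, so T0 costs would predate the patient's admission and not necessarily the training.

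Fourth, imbalance under random allocation of matched departments is centred on zero, and an interval that respects clustering already reflects it. That is right for departments. It is not assured for patients, whom unblinded staff admit to the study after allocation.

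**Conclusion.** The point holds as a weakness in how the cost estimand is written. The cost difference and the ICER numerator carry no baseline covariate, in a trial whose departments differ widely, are imperfectly matched, and enrol patients after allocation through staff who know the arm. Taken as written, precision is lost and baseline differences from chance or selection stay in the cost results.

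The size cannot be determined from the article. The range of about 1% to 20% of interval width assumes r of 0.3 to 0.6; the lower end also assumes a cost ICC of 0.2 with no shrinkage at department level. It would be tempting to quote only 5% to 20%, but that needs the same correlation at department level, which nothing in the article establishes. Nor does the article demonstrate systematic bias: selection is a possible route, not a shown one. The sample size of 423 is unaffected.

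**What to change.** - Estimate the cost difference from a multilevel regression of total costs on arm, adjusted for T0 TiC-P costs if these are collected at T0. State whether they are.
- If they are not, adjust for the matching factors (main diagnosis and average treatment duration), department type, and T0 EQ-5D and BSS. Say how the three departments without a recorded duration are handled.
- Refit the model within each bootstrap replicate and each imputed dataset, and use the adjusted difference for the interval, the ICER and the acceptability curve.
- Report unadjusted mean costs per arm as description.

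Fixing this before the data are seen also prevents a later choice between an adjusted and an unadjusted ICER. The change needs a few sentences and slightly more programming; the fallback covariates need no new data. The drawback is dependence on a regression model for skewed costs. Adjustment is also only a partial remedy for selection at entry, since it removes differences in what was measured and no more.

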## Discussion

This article describes the study protocol of a multicentre cluster RCT examining the additional effect of a multifaceted TtT-e program on suicide ideation with usual guideline implementation (IAU). Secondary outcomes are number and intensity of non-fatal suicide attempts, treatment satisfaction, cost-effectiveness, and cost-utility.

We hypothesize that, as a result of the improved skills and confidence of health care professionals due to IAU plus the TtT-e program, suicidal patients will recover more quickly from suicidal ideation and will show fewer suicide attempts as compared with patients in the control condition. Also, we hypothesize that patients from departments allocated to the experimental condition will show more treatment satisfaction. Additionally, we expect that IAU plus the TtT-e program will be more cost-effective compared to IAU.

To date, the evidence on effective strategies to implement guidelines in mental health care is scarce. If the study hypotheses are confirmed, the TtT-e program could be more widely distributed and applied in mental health care, reducing suicidal behaviors and limiting the costs due to suicidal behaviors.

A strength of this study is that data are collected in a naturalistic setting and hypotheses are examined in a RCT design. A further strength is the size of the study in which various MHIs and patients of miscellaneous diagnostic categories are included. We suggest that the patient flow within these 43 departments fairly represents the Dutch patients in mental health care. Of the 30 large MHIs in The Netherlands that were approached for the study, 10 were included in the study. From the many hundreds of psychiatric departments within these 10 MHIs, 43 departments joined the study. Patient diagnoses range from affective disorders, personality disorder, to addiction disorder. Among the 43 departments are long-stay, crisis, and inpatient and outpatient departments. The age of patients range from 18 to over 80 years. Figure 
1 demonstrates that the included departments are located in urban and rural regions of The Netherlands. We conclude that the included departments provide a representative sample of all departments in mental health care institutions in The Netherlands. We will compare the patient characteristics of the sample with the national patient population available via the Dutch Association of Mental Health and Addiction Care (GGZ Nederland, Amersfoort, The Netherlands), and will describe the results to check external validity.

A possible limitation of the study is that budget cuts, reorganizations, and layoffs, commonplace in Dutch mental health care, may interfere with the study aims. Attrition of patients to the study is a further challenge, since not all patients will complete the ROM at all intervals due to the lack of time of professionals or inexperience with the ROM
[37]. Using a strict protocol and local research assistants/nurses, we aim for limited drop-out. To prevent drop-out, research assistants will help patients to complete the questionnaires and will make appointments for follow-up assessment.

Commitment of both management and employees of the participating MHIs is crucial. To date, willingness of both management and employees to apply the TtT-e program is excellent. The findings from the current study may be generalized to implementation of other (mental) health care guidelines.

## Trial status

Ongoing patient recruitment.

## Abbreviations

BSS: Beck Scale for Suicidal Ideation; CASE: Chronological Assessment of Suicidal Events; DIF: differential item functioning; IAU: implementation as usual; ICER: incremental cost-effectiveness ratio; MHI: Mental health institution; NIP: Dutch Association of Psychologists; NVvP: Dutch Association of Psychiatrists; PGSB: Practice guideline on the assessment and treatment of suicidal behavior; PITSTOP suicide: Professionals in training to STOP suicide; QALY: Quality-adjusted life year; RCT: Randomized controlled trial; ROM: Routine outcome monitoring; TiC-P: Trimbos questionnaire for costs associated with psychiatric illness; TtT-e: E-learning supported train-the-trainer implementation; V&VN: Dutch Nurses’ Association; VAS: Visual analogue scale.
